## Abstract

**Introduction:**

Atrial fibrillation (AF) is the most common arrhythmia globally. It is associated with a fivefold risk in stroke, but early diagnosis and effective treatment can reduce this risk. AF is often underdiagnosed, particularly in low-income and middle-income countries (LMICs) where screening for AF is not always feasible or considered common practice in primary care settings. Epidemiological data on AF in LMICs is often incomplete particularly in vulnerable populations. This LMIC research collaborative aims to identify the prevalence of AF in the Northern Sri Lankan community.

**Methods and analysis:**

A cross-sectional household survey piloted and codesigned through a series of community engagement events will be administered in all five districts in Northern Province, Sri Lanka. A multistage cluster sampling approach will be used starting at district level, then the Divisional Secretariats followed by Grama Niladhari divisions. Twenty households will be selected from each cluster. The study aims to recruit 10 000 participants aged 50 years or older, 1 participant per household. Demographic and socioeconomic characteristics, well-being and lifestyle and anthropometric measurements will be collected using a digital data platform (REDCap, Research Electronic Data Capture) by trained data collectors. Participants will be screened for AF using a fingertip single-lead ECG via a smartphone application (AliveCor) with rhythm strips reviewed by a consultant cardiologist. Prevalence of AF and risk factors will be established at province and district-levels. Adjusted ORs and population attributable fractions for AF risk factors will be determined.

**Ethics and dissemination:**

This study was approved by the Ethics Review Committee of Faculty of Medicine at University of Jaffna. Written informed consent will be obtained from all participants. Findings will be disseminated through publication in a peer-reviewed journal and presentations at conferences. The findings will enable early treatment for new AF diagnoses and inform interventions to improve community-based management of AF in LMICs.

Strengths and limitations of this studyThis study uses mHealth (mobile health) technology that has the ability to quickly and efficiently identify atrial fibrillation (AF) within resource-limited settings.The use of a near-real time data collection tool and analytical dashboard will enable the ability to identify and rectify any data collection issues as the study progresses.Conducting the study in this low-income and middle-income countries setting will inform future non-communicable screening policies to extend the evidence base beyond high-income settings.While data pertaining to a variety of risk factors will be collected, the temporal relationship between risk factors and AF will not be attained.Given the cross-sectional study design, incidence of AF and other non-communicable diseases will not be feasible.

## Introduction

Atrial fibrillation (AF) is the most common cardiac rhythm disorder globally.^1^ AF prevalence is increasing worldwide with age, male sex, hypertension, diabetes and heart disease as major risk factors.^2^ AF is associated with a fivefold increase in stroke and over 25% of the strokes are due to AF.^3^ Early identification and effective management of AF can prevent strokes and contribute to improved management of cardiovascular health.^3–5^ Stroke caused by AF is largely preventable with appropriate use of oral anticoagulant therapy, a therapy which is readily available in health systems internationally.^5^ However, an estimated 33% of the people with AF are asymptomatic, meaning many people with AF remain undiagnosed until they present with life threatening complications.^6^

Screening for AF in people aged 65 years or older is now recommended by some clinical practice guidelines and is common place in general practice in upper-middle and high-income countries.^7 8^ Such population screening has in part been made possible by the successful development and scale up of smartphone technologies, which enable rapid point of care diagnosis through opportunistic pulse palpation or ECG rhythm strip.^9 10^

Such practice remains limited in low-income and middle-income countries (LMICs), where cardiovascular diseases are being increasingly reported in younger populations (aged 50 years and above), and which are rapidly attributing to causes of mortality.^11–14^ Chronic disease prevalence in this relatively young population appears as a result of both childhood conditions such as rheumatic fever and valvular heart disease, and early onset of diabetes and hypertension as a result of age and lifestyle-related factors.^11 15^ Additionally, complications associated with non-communicable diseases are attributed with worse outcomes and greater morbidity for people living in LMICs when compared with high-income settings.^16^ Despite this disparity in diagnosis, management and outcomes, there is limited high quality epidemiological data on AF in LMICs, specifically in South Asia.^2 15^

Screening programmes in the regions are hindered by poor recruitment, often as a result of poor community engagement and low levels of non-communicable disease-related health literacy. Where programmes do exist, vulnerable groups are often under-represented and missing or incomplete data inhibits meaningful interpretation of data.^17^ Epidemiology researchers are increasingly looking to social science and implementation strategies to engage communities in research design to ensure they are included in such programmes. Particularly in LMICs, it is imperative to overcome these known barriers to study implementation and ensure that study findings are not only disseminated back to communities, but are both acceptable to and used by healthcare providers.

This study aims to implement an AF screening programme using smartphone technology, feasible for delivery at scale in resource constrained LMIC settings. Specifically, we aim to determine the prevalence of AF and associated risk factors in Northern Province, Sri Lanka, and to evaluate the feasibility and acceptability of smartphone-enabled single-lead ECG for the purpose of diagnosing AF.

## Methods and analysis

### Research design

This cross-sectional study combines a household questionnaire and an onsite assessment of the presence of AF using a single-lead ECG reader on a digital mobile health (mHealth) platform. The study commenced in June 2020 and is expected to be complete by March 2022.

### Study setting

This study is being conducted across all five districts in the Northern Province of Sri Lanka: Jaffna, Kilinochchi, Mannar, Mullaitivu and Vavuniya. Each district is divided into administrative units called Divisional Secretariats (DS). Each DS is further divided into many Grama Niladhari (GN) divisions. Each GN division is identified by a unique number. Northern Province is located just 22 miles (35 km) southeast of India and has approximately 1.3 million permanent residents.^18^ Its climate is typically tropical, but with a hot dry season from February to September. While the Northern Province was heavily impacted by 30 years of conflict, the province has recently opened to the global market and its share of provincial gross domestic product is increasing.^19^ Publicly available healthcare including medical appointments, medications and medical procedures are free to all Sri Lankan citizens.

### Sampling and sample size

Consistent with other LMIC studies and in response to the increasing literature on morbidity and chronic disease prevalence in South Asia, we selected a threshold of 50 years and above for inclusion in screening, a lower than current recommended practice of 65 years.^12^ Therefore, individuals aged 50 years or above will be considered eligible; additionally, they must be fluent in the Tamil language. Based on already published methods,^20^ anyone suffering from terminal illnesses, in need of immediate hospital admission or currently an inpatient in a hospital setting will be excluded. All data collectors—which includes a medically trained doctor and two nursing graduates—will be trained to assess individuals for eligibility.

This study will use a multistage cluster sampling approach. The multistage process will start at the district level, then to the DS level followed by the GN level. GN divisions will then be divided into clusters based on population size and from these clusters, a single cluster will be selected at random. Each cluster will consist of 20 households, one participant per household. We will first randomly select an index house within each cluster and from the index house, 20 households on the right side will be selected. In households where more than one eligible person lives, the person with a birthday closest to the date of visit will be selected. We used 2012 population census data to select the clusters and index house within each cluster.^19^

For the sample size calculation, the prevalence of AF in Sri Lanka was estimated to be 1% based on previous evidence.^2 21 22^ We used a design effect of 2 to adjust for cluster sampling, and we used an alpha level of 5% and beta level of 20%. We increased our sample size by 10% to account for non-participation,^23^ leading to a minimum sample size of 10 000 participants required.

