### Statistical methods

A direct standardisation technique will be used to obtain province-level prevalence data from the district level results. The proportion of the population exposed to known risk factors of AF will be calculated. Prevalence of risk factors in participants with established, without and with newly diagnosed AF will be determined. Multivariate logistic regressions will be used to calculate adjusted ORs for AF risk factors. Population attributable fractions will be calculated for risk factors that were included in the logistic regression model. Statistical analysis would be carried out using SPSS V.23 (IBM Corp. 2015; Armonk, New York, USA). Raw data will be reported along with scores from assessment tools (eg, GAD-2 and PHQ-2), derived using published definitions. All calculations will be published with open access, ensuring reproducibility of study findings.

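### The 10% allowance for non-participation protects precision only, and the one stated prevalence adjustment is by district, so any age or sex imbalance among participants stays in the estimates

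*Protocol article*

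**What the plan says.** Sampling and sample size (Protocol article) assumes that "the prevalence of AF in Sri Lanka was estimated to be 1% based on previous evidence", applies a design effect of 2, and then states: "We increased our sample size by 10% to account for non-participation", "leading to a minimum sample size of 10 000 participants required". No other statistical handling of non-participation is given.

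Statistical methods names one adjustment of prevalence: "A direct standardisation technique will be used to obtain province-level prevalence data from the district level results". It mentions no age or sex stratum and no non-response weight. It adds that the proportion exposed to known risk factors will be calculated, without weighting. The logistic regression adjusts odds ratios, not prevalence.

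The Introduction states: "AF prevalence is increasing worldwide with age, male sex, hypertension, diabetes and heart disease as major risk factors". The Abstract promises prevalence of AF and of risk factors at province and district level.

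**The concern.** A larger sample narrows the interval but does not change who is in it. Standardising from district to province corrects the balance between districts and leaves the mix within each district as recruited. If older people, or men, take part less often than others, both the district figures and the province figure built from them are shifted. The article itself names age and male sex as major AF risk factors, so these are the obvious variables to balance on.

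This concerns response, not selection. It would remain even if every eligible resident had the same chance of being picked. Prevalence is the study's main product, and risk-factor prevalence is one of its stated outputs.

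**Working it through.** **The plan's own figure.** The article gives 1% prevalence, design effect 2, alpha 5%, beta 20% and a 10% increase, but no precision or detectable difference, so 10 000 cannot be re-derived. Read as a precision calculation, 10 000 = 1.96² × 0.01 × 0.99 / d² × 2 × 1.1 gives d = 0.29 points. That is a separate matter. What counts here is that the factor 1.1 acts on the width of the interval and nowhere else.

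**Sampling error at n = 10 000.** SE = √(2 × 0.01 × 0.99 / 10 000) = 0.141 points; 95% half-width = 1.96 × 0.141 = 0.28 points.

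**Bias model (all cell values are assumptions).** Population aged 50+: men 50–64 30%, women 50–64 35%, men 65+ 15%, women 65+ 20%. AF prevalence in the same order: 0.6%, 0.4%, 2.4%, 1.6%. True value: 0.18 + 0.14 + 0.36 + 0.32 = 1.00%.

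Expected estimate = Σ(share × participation × prevalence) / Σ(share × participation).

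| Assumed participation | Overall | Expected AF estimate | Bias (points) |
|---|---|---|---|
| 90% in every cell | 90% | 0.900/0.900 = 1.00% | 0 |
| 65+ 75%, younger 100% | 91% | 0.830/0.9125 = 0.91% | −0.09 |
| 65+ 70%, younger 95% | 86% | 0.780/0.8625 = 0.90% | −0.10 |
| 65+ 60%, younger 90% | 80% | 0.696/0.795 = 0.88% | −0.12 |
| Men 50–64 55%, women 50–64 80%, men 65+ 90%, women 65+ 95% | 77% | 0.839/0.770 = 1.09% | +0.09 |

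Sample size does not appear in the formula, so the 10% increase leaves the bias as it is. If the pattern is the same in every district, each district estimate has the same expectation. A weighted mean of equal values is that value, so district standardisation also leaves it as it is. Standardising by age and sex returns 1.00% in every row, provided participation is unrelated to AF within cells.

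A bias of 0.10 points is 0.10/0.141 = 0.71 SE. Coverage of the nominal 95% interval is then Φ(1.96 − 0.71) − Φ(−1.96 − 0.71), or about 89%.

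**Sex-linked risk factor.** Assume tobacco use of 40% in men and 2% in women, with 45% men: 0.45 × 40 + 0.55 × 2 = 19.1%. In the last row of the table, men make up (0.165 + 0.135)/0.770 = 39% of participants, and the estimate is 16.8%. The bias is 2.3 points. With design effect 2, the half-width is 1.96 × √(2 × 0.191 × 0.809 / 10 000) = 1.09 points, so the bias is about twice the half-width.

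A milder pattern, with men at 85% and women at 94% (90% overall), gives a male share of 0.3825/0.8995 = 42.5% and an estimate of 18.2%. That bias of 0.9 points is inside the half-width.

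**The case against.** The strongest objection is that Statistical methods is one condensed paragraph in a journal article. It names no strata, does not exclude age and sex, and a fuller analysis plan may include them. Inflating the sample for non-participation is also ordinary practice, and the article does not claim that this removes bias. Both points stand. No sentence is contradicted, and the case is for a better-specified method than the one written down.

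Four stronger readings are tempting, and the documents do not support them:

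- *That the plan ignores non-participation.* It describes community volunteers, engagement workshops, leaflets revised after the pilot, and dashboards showing recruitment and reasons for failure to consent. These may raise or monitor participation, although no step carries them into the estimates.
- *That uneven participation by age and sex is to be expected.* The Introduction says that "Screening programmes in the regions are hindered by poor recruitment" and that vulnerable groups are often under-represented, but this describes other programmes and does not mention age or sex. The COVID-19 section reports adapted procedures and no effect on participation.
- *That AF prevalence will be badly wrong.* The AF bias in these patterns is smaller than the sampling error, its direction is unknown, and several patterns imply overall participation below the roughly 90% planned for. At 90% overall, the 39% male share in the tobacco example would need nearly every woman and only about 78% of men to take part.
- *That crude differences between districts are a bias.* Suppose AF is 0.5% under 65 and 2% at 65+ in two districts, with 30% and 40% of people aged 65+. Their prevalences are 0.7 × 0.5 + 0.3 × 2 = 0.95% and 0.6 × 0.5 + 0.4 × 2 = 1.10%. Those are the true burdens, and weighting each district to its own census returns them unchanged.

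**Conclusion.** The point holds in a conditional and modest form. Neither the 10% increase nor standardisation from district to province, followed as written, removes an age or sex imbalance within districts. If participation is even, there is no bias. If it is uneven in the ways assumed, AF prevalence moves by about 0.1 points (roughly 10% in relative terms), inside the 0.28-point half-width. Prevalence of a strongly sex-linked risk factor can move by more than its half-width, which makes risk-factor prevalence the stronger reason to act. These sizes rest on assumed cell shares, prevalences and participation rates, on the AF design effect of 2 also applying to tobacco use, and on participation being unrelated to AF within age-sex cells. This is an inexpensive improvement to the stated method; it does not show that the results will be wrong.

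**What to change.** In Statistical methods, state that:

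- prevalence of AF and of risk factors will be weighted (directly standardised) by age band and sex within district to the population aged 50 or over, using the most recent census or official population estimates available;
- the province figure will be the sum over these cells, with sparse cells merged;
- crude figures will be shown alongside.

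If districts are to be compared, also give figures standardised to one common age-sex population, because weighting each district to its own census leaves differences in age structure in place. Report participation by age and sex where these were recorded. Fieldwork began in June 2020, so this may be incomplete for people who refused earlier.

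The change is mainly analysis wording and uses age and sex from the survey plus population counts. The variance rises slightly. The only census named is from 2012, eight to ten years before data collection, so its age structure may be dated. It also counts people who are not eligible, such as those not fluent in Tamil, current inpatients and the terminally ill. Weighting will not correct for participation that depends on AF itself within an age-sex cell. If a fuller analysis plan already uses these strata, adding them to the text is enough.

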### Pilot study

The data collection tool was piloted in 100 households located in a GN division that will not be included within the main study. The pilot study comprised participants from varying socioeconomic backgrounds and education levels. Participants were asked to give their perspectives on acceptability of participating in the study including the duration of the interview, ease of understanding the interviewer administered questionnaire and their experience of using the fingertip rhythm assessment ECG application. Additionally, data collectors fed back on the challenges they experienced in collecting the data and reported on their perception of participants’ willingness to participate and recall, internal consistency reliability and inter-rater reliability of the questionnaire. During the piloting of the questionnaire, participants’ questions and concerns were noted and reported through the electronic data collection tool used; these were reviewed daily by the principal and co-investigators.

Feedback following the pilot revealed (1) data collector concerns regarding availability of and access to clinical books for relevant medical history, (2) participant concerns regarding future use of fingerprints, reasons for the survey and being disadvantaged if they were found to have AF and (3) participants understanding of medical prescriptions. In response, we made the following adaptations to the study conduct protocol prior to commencing data collection: reporting of medical history will be reported as either being directly observed from clinical books or via participant recall; medications will be reported by categories for simplicity and; an update of participant information leaflets to ensure the aim of the study, data security and what happens after the study is clear. Additionally, further training for the data collection team was provided on the management of personal information, the AliveCor device and how to respond to participant concerns.

### Data collection

The household survey comprises five sections: (1) demographics and socioeconomic profile; (2) current and past health conditions; (3) well-being and lifestyle; (4) anthropometric measurements and; (5) screening for AF. The demographic and socioeconomic profile will be collected using the Sri Lanka Demographic and Health Survey 2016 questionnaire which includes education levels and occupation.^24^ Current medical conditions and medical history of comorbid diseases will be collected using the Charlson Comorbidity Index^25^ along with the recording of any current medications prescribed by physicians or indigenous healers. To assist participant’s recalling their medical history, the data collection team will advise them to review their clinical books which is a paper notebook provided by the health system and commonly kept by patients who see clinicians for long-standing conditions in which clinical appointments, clinical assessments, investigations and medications are often detailed. Well-being and lifestyle assessment will be collected using the following validated instruments: General Anxiety Disorder-2 (GAD-2) scale,^26^ Patient Health Questionnaire-2 (PHQ-2),^27^ International Physical Activity Questionnaire—Short Form,^28^ Audit C for alcohol use,^29^ WHO STEPS instrument^30^ for assessing tobacco use, Berlin Questionnaire for sleep quality,^31^ EQ-5D-5L (EuroQol-5 dimensions-5 levels) for quality of life,^32^ and the Fried Frailty Index.^33^ Diet will also be assessed by asking questions on consumption levels of relevant food groups.^34^ Participants will be asked to describe their usage of healthcare services in the preceding year, including with public and private services and indigenous healers. Anthropometric measurements will include the recording of each participant’s weight, height, waist and hip circumference along with their blood pressure (measured by data collectors). The household survey will take approximately 45 min per participant.

Participants will have their heart rhythm recorded using fingertip electrodes which activate a bipolar single-lead (lead 1) ECG recording through a smartphone application (AliveCor) that uses an automated algorithm to interpret the cardiac rhythm and identify AF.^35^ AliveCor is a validated tool used internationally and is Food and Drug Administration approved.^36 37^ Most studies have found the sensitivity and specificity of AliveCor to be 90% or above.^36^ The application logs the participants anonymously, assigning a unique ID to each participant and stores a report of the rhythm detected. The participant’s unique ID is entered into the data collection tool to enable linkage of the participant’s heart rhythm results and their questionnaire data. Reports of the single-lead recording (AliveCor report) will be downloaded and reviewed by a consultant cardiologist off-site who will determine the outcome of the test. Any participant with a positive or undifferentiated AliveCor results will be referred to see the study consultant cardiologist and have a 12-lead ECG and relevant assessment. A member of the research team will follow-up with participants that had not visited the hospital within 3 months following referral. Patients access services through the existing government health service.

Digital data collection tools that had been developed and successfully deployed in Sri Lanka were adapted for use in this study.^38^ We improved data quality and standardised terminology for diagnosis and comorbidities and included automatic data-logic checks for numerical values to reduce data entry errors. The final tool, using the REDCap (Research Electronic Data Capture)^39^ software, includes satellite mapping and inbuilt date and time stamps and supports study coordinators with monitoring data collection and feedback. Data collected is automatically transferred to analytical dashboards (figure 1); thus, the study research team has in near-real time access to study recruitment, data quality, reasons for failure to consent and feasibility of study components. The digital tool is accessible via a mobile device and includes offline functionality, enabling the ability to overcome any issues with mobile data coverage.

